### Sample size

The primary outcome of this experiment is the PSQI score, and a two-sample t test for superiority by a margin will be adopted. Similar published studies have indicated that the mean PSQI scores of the EA and SA groups are 9.8 and 13.9, respectively, with standard deviations of 3.1 and 3.2. The SA group is expected to have a higher score than the EA group, with an expected score difference of 1.5. With a significance level of α = 0.025, power of 1-β = 0.9, and equal sample sizes of the SA and EA groups [21], the minimum sample size was calculated. According to the preset parameters, the “Two-Sample t Tests for Superiority by a Margin Allowing Unequal Variance” option in the Means menu of Power Analysis and Sample Size software (PASS; version 11; NCSS Statistical Software, Kaysville, UT, USA) was used for sample size calculation. A sample size of 32 was calculated for both groups. Considering a dropout rate of 20%, each of the three groups would require 40 participants. Therefore, 120 subjects will be included in the study to ensure the accuracy and scientific validity of the research results.

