### Statistical analysis

In general, statistical involve a two-tailed approach, and any results that have a p value of less than 0.05 are considered statistically meaningful. Continuous data will be characterized by the mean ± standard deviation, median, highest value, and lowest value, while count and ordinal data will be represented via counts and percentages. The type of analysis used for between-group comparisons depends on the data distribution: paired-sample t tests or nonparametric tests will be used for continuous data, chi-square tests or Fisher’s exact test will be used count data, and nonparametric tests will be used for ordinal data. For comparisons of baseline values, paired-sample t tests or nonparametric tests will be used for continuous data, and nonparametric tests will be used for count data.

All EEG data will be processed using MATLAB (MathWorks, Inc., Natick, Massachusetts, USA). Graph theory analysis will be performed using the Gretna toolbox based on MATLAB. The analysis of brain network topological properties will employ graph theory methods. Specifically, the following steps will be used: segmentation according to the AAL template to divide the brain into 116 regions, computation of the average BOLD time series signals within each region, and calculation of Pearson correlation coefficients between each pair of regions. It will yield a 62 × 62 correlation matrix. The correlation matrix will then be converted into a binary matrix by applying a threshold r value (Pearson correlation coefficient) to construct a brain network. The topological properties of the brain network, including global efficiency, local efficiency, node degree, and node betweenness centrality, will be analyzed. Additionally, the relationships of topological properties with cognitive function and sleep quality scores will be examined through correlation analysis.

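### The distribution-dependent (and paired) test in the analysis section is not the two-sample t test with a margin on which the PSQI sample size rests, and nothing fixes one PSQI test across visits

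*Protocol article*

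**What the plan says.** The Statistical analysis section of the protocol article sets a general rule: "The type of analysis used for between-group comparisons depends on the data distribution". Its options are these: "paired-sample t tests or nonparametric tests will be used for continuous data, chi-square tests or Fisher’s exact test will be used count data". For ordinal outcomes, "nonparametric tests will be used for ordinal data". No normality criterion is given, no rank test is named, and the choice is not fixed by outcome or visit. The section works at a two-tailed 5% level and mentions no margin.

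The Sample size section is specific: "The primary outcome of this experiment is the PSQI score, and a two-sample t test for superiority by a margin will be adopted". The software option it cites is "Two-Sample t Tests for Superiority by a Margin Allowing Unequal Variance". Its inputs are that "the mean PSQI scores of the EA and SA groups are 9.8 and 13.9, respectively", SDs of 3.1 and 3.2, a figure of 1.5 points, alpha 0.025 and power 0.9. These give 32 per group, raised to 40 for 20% dropout.

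Table 1 schedules the PSQI at Weeks 0, 4, 8 and 20, so there are three post-baseline comparisons. The Outcomes section lists the PSQI as secondary, whereas the Sample size section calls it primary. That is a separate matter, and the present point holds either way.

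**The concern.** Two sections of the same article prescribe different analyses for the same score, in three respects.

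- **Independence.** A paired test needs a natural pairing of observations. Patients randomised 1:1:1 to separate arms have none, so a paired test between arms would depend on an arbitrary ordering.
- **Margin.** The sizing tests whether electroacupuncture beats sham by more than 1.5 points. The analysis rule, as written, tests whether there is any difference.
- **Contrast.** A t test addresses a difference in means and a rank test addresses a shift in ranks. If the data choose at each comparison, Weeks 4, 8 and 20 may rest on different contrasts, and a rank result cannot be set directly against 4.1 or 1.5 points.

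At stake is whether a significant PSQI result means what the sample size section says it would mean, and whether the reader can be sure that the test was settled before the data were seen.

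**Working it through.** **1. Reproducing the plan's figure.** Inputs from the Sample size section: means 9.8 and 13.9, so the difference is 13.9 − 9.8 = 4.1; SDs 3.1 and 3.2; margin 1.5; one-sided alpha 0.025; power 0.9.

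- Distance from the margin: 4.1 − 1.5 = 2.6.
- Standard error with 32 per arm: √(3.1²/32 + 3.2²/32) = √(0.3003 + 0.3200) = 0.788.
- Welch degrees of freedom about 61.9; critical value 1.999.
- Noncentrality: 2.6/0.788 = 3.30. Power from the noncentral t: 0.901. With 31 per arm it is 0.892.
- Dropout: 32/0.8 = 40 per arm, and 3 × 40 = 120.

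So 32 is right for an independent two-sample unequal-variance t test with a 1.5-point margin. The other readings tried, also with t tests, do not return 32:

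| Reading | n per arm |
|---|---|
| Difference 4.1, no margin | 14 |
| 1.5 taken as the true difference | 94 |
| Margin 1.5, alpha 0.025 two-sided | 38 |

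**2. What losing the margin changes.** A two-sided 5% t test and a one-sided 2.5% t test share the same critical value in the direction of benefit. The substantive difference is therefore the margin, not the alpha.

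- Smallest significant observed difference without a margin: 1.999 × 0.788 = 1.57 points.
- With the margin: 1.5 + 1.57 = 3.07 points.
- Chance of significance at a true difference of 1.5, no margin: noncentrality 1.5/0.788 = 1.90, giving 0.466, about 47%. In the test used for sizing, 1.5 is the null boundary and the chance is 2.5%.

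**3. How often the test might switch.** The protocol names no criterion, so a Shapiro-Wilk test at 5% in each arm is assumed, with 32 per arm and visits treated as independent.

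- Unrounded normal scores (5% flagged per arm): 1 − 0.95² = 9.8% per comparison; 1 − 0.95⁶ = 26% for at least one switch over three visits.
- Integer scores from rounded normals (simulated flag rates 9.4% and 8.5%): 1 − 0.906 × 0.915 = 17.1% per comparison; 1 − 0.829³ = 43% over three visits.

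Correlation between visits of the same patients would lower the three-visit figures.

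**4. What the switch does to error and power.**

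- Type I error of a mechanical two-stage rule, PSQI-like null data, nominal 5%: 4.7% and 5.4% in separate simulation runs.
- At the planned means, with no margin, the t and rank tests disagree on significance in about 0.1% of trials or fewer.
- Power against the 1.5 margin, normal data: Welch 0.91, rank-sum 0.89, two-stage 0.91. With an assumed skewed distribution (gamma, shape 2): Welch 0.89, rank-sum 0.96.

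**The case against.** The strongest reply is that choosing a parametric or nonparametric test by distribution is customary shorthand in a condensed article, that the normality criterion normally belongs in a statistical analysis plan, and that paired-sample may be a slip. A missing criterion would indeed be no finding. What stands against the reply is that the article does not merely omit detail. It states a rule and a test that differ from those in its own Sample size section.

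It can also be said that the PSQI is plainly handled as continuous, since it is sized by mean and SD. That is accepted, so this point does not rest on the rule for ordinal data. Means, SDs and medians will be reported whichever test is used, so a PSQI-point difference could still be read off. That softens the loss of interpretability, but such a difference would carry no matching test or interval.

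A reader might infer that the rule inflates false positives. The figures do not support that: a mechanical switch stays near 5%. Rates of 5.5% to 6.8% arise in simulation only if the analyst takes the smaller of two p values. The protocol does not allow that, because the distribution decides, and it blinds those doing the statistics to allocation.

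A reader might also infer that a data-driven switch has no merit. With strongly skewed scores the rank test has more power (0.96 against 0.89), so that claim fails too.

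**Conclusion.** The point holds as a conflict between two sections. As written, the PSQI analysis is not the test the trial was sized on, because the t option is paired, the margin is absent and the distribution may replace the contrast. The largest consequence is the margin: at a true difference of 1.5 points the chance of significance is about 47% instead of 2.5%, assuming normal scores, the stated SDs and 32 evaluable patients per arm.

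The switch between tests matters less. Under the assumed pre-test it could affect at least one of three visits in roughly 26% to 43% of trials, but with negligible effect on type I error and, for near-normal scores, on power. Its harm is to consistency across visits, pre-specification and interpretation.

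Two stronger conclusions should not be drawn. The sample size is not wrong: 32, 40 and 120 all reproduce. Nor do the planned tests of baseline values ("For comparisons of baseline values, paired-sample t tests or nonparametric tests will be used for continuous data") undermine any treatment result. They are uninformative in the randomised Study 2 but legitimate in Study 1, which compares non-randomised patients and controls.

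**What to change.** - **PSQI.** Replace the distribution-dependent rule by one pre-specified independent-groups comparison of means, used at every visit. Report the PSQI-point difference with its 95% confidence interval, and claim superiority only if the sham-minus-electroacupuncture interval lies wholly above 1.5, which matches one-sided 0.025. If no margin is intended, restate the Sample size section instead. Keep a rank test as a sensitivity analysis only.
- **Wording.** Change paired-sample to two-sample wherever arms are compared.
- **WCST and EEG measures.** Name one test per outcome in advance. It need not be mean-based, since some of these measures may be skewed.
- **Baseline in Study 2.** Presenting values by arm descriptively is optional and minor.

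The cost is wording only. No patients, visits or data are added, and 32 evaluable (40 randomised) per arm stays at 90.1% power. The downside is some loss of power if PSQI scores prove strongly skewed, which the sensitivity analysis would show.

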### Ethics and dissemination

The experimental protocol follows to the principles of the Declaration of Helsinki and has been approved by the Ethics Committee of the First Affiliated Hospital of Guangdong Pharmaceutical University (Medical Ethics Review [2021] No. 49). Modifications to the protocol will be reported. Researchers will receive instructions to provide trial information to qualified patients and obtain written informed consent if they agree to participate. The trial results will be published in peer-reviewed journals and made available to the media and the public.

## Discussion

Currently, the construction of functional brain networks mainly relies on techniques such as electroencephalography (EEG), magnetoencephalography (MEG), and functional magnetic resonance imaging (fMRI), combined with complex network analysis methods based on graph theory. These methods aim to reveal the topological principles of brain networks and the underlying mechanisms of brain function.

fMRI is an essential method for exploring brain networks, with the advantages of high spatial resolution and the ability to detect deep brain tissue activity. However, its temporal resolution is limited, resulting in a time delay between neuronal synchronization and the occurrence of relatively sharp wave discharges. DePasquale et al. [22] divided collected MEG data into 10-second time windows for separate data analysis, revealing significant differences in network connectivity within each time window. Different brain networks were active in various time windows, and several brain networks were sometimes activated simultaneously. This study suggested that fMRI research may overlook dynamic changes in brain networks due to its low temporal resolution. This highlights that recent fMRI-based brain network studies have focused on exploring static brain network topology within specific periods. Researchers have increasingly focused on constructing dynamic brain functional networks at short time scales, such as continuous time points, to better understand temporal changes and real-time brain activities.

Moreover, using different statistical approaches when processing fMRI data can lead to significant differences in research outcomes, raising questions about many past fMRI research conclusions [23, 24]. In general, brain functional network research using fMRI technology has become increasingly mature. However, its temporal resolution is still relatively low, and due to issues related to the choice of statistical methods, more evidence is needed regarding the use of fMRI to study brain networks.

This study has certain limitations. First, as acupuncture cannot be performed blindly, we will endeavor to minimize the impact by providing comprehensive training to the practitioners, which included standardized communication with the subjects. Second, we will not collect event-related potentials to evaluate specific cognitive functions. Third, the extended period of the study will likely lead some individuals to drop out.

### Trial status

This study was officially registered with the Chinese Clinical Trial Registry on 20 May 2022 with the registration ID ChiCTR2200060150. Recruitment of participants began on 1 September 2022 and is scheduled to be completed by the end of December 2024. In the event of any modifications to the protocol, we will inform the investigators, ethics committee, and trial registries.

## Data Availability

As stated in the informed consent form, the subject’s personal information will be kept private and not shared with the public unless the subject has given their consent. When needed, the ethics committee or project funding department can access the subject’s data for consultation. No other use of the subject’s information or disclosure of it to other groups is allowed without their permission.

## List of abbreviations

EEG: electroencephalography
DLPFC: dorsolateral prefrontal cortex
MPFC: medial prefrontal cortex
WCST: Wisconsin Card Sorting Test
PSQI: Pittsburgh Sleep Quality Index
DSMB: Data and Safety Monitoring Board
EA: electroacupuncture
SA: sham acupuncture
MEG: magnetoencephalography
fMRI: functional magnetic resonance imaging
